### Sub aim 1b

To improve overall health status and the ability of patients to attend scheduled clinic visits in rural settings, a new approach to solving rural health disparities is needed. The objective for this Sub aim 1b is to evaluate the feasibility, acceptability, and outcomes of care using mI SMART. To attain the objective for this aim, we will test the feasibility and acceptability of mHealth care delivery through identification of at-risk patients and measure outcomes of care, including patient–provider communication, adherence to treatment, self-management ability, quality of life, blood glucose, blood pressure, and weight. We will give at participants an Android tablet, a Bluetooth enabled glucometer, blood pressure cuff, and scale along with a training session on how to use the devices. The replacement of broken or damaged equipment will be managed by the project coordinator and sent to participants via postal mail or patient pick-up at the clinic. We will pursue an approach of combined activity logging and questionnaires to evaluate provider communication, adherence to treatment, feasibility, and acceptability. We will use a pre/post design with no randomization or control group. Because of budgetary constraints, we will enroll 30 participants into the study. A larger randomized control trial is planned after analysis of the results of this study.

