### Feasibility and acceptability

The use of the developed technology to deliver the intervention and to collect and store data will be evaluated in four ways. We will assess the ability of participants to use the developed technology to receive and transmit health information by: (1) reviewing the presence or absence of data in the database from each participant, (2) assessing the electronic activity logs and error messages for each participant, (3) assessing the electronic activity logs and error messages for each provider (4) analyzing the electronic activity logs of each application for number of times each application was used as well as common errors. Lastly, we will assess the acceptability of the technology with post intervention electronic patient and provider satisfaction questionnaires.

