### Patient–provider communication and satisfaction

Participants will be provided questionnaires to assess communication based on 5-point Likert scale. We will evaluate ease and convenience of communication, promptness of replies, quality and amount of information, and quality of care. In addition, participants will assess their satisfaction with the overall system. The provider’s communication and satisfaction will measure the amount of time to review electronic logs and reply to electronic messages, their promptness in responding to messages, volume of messages, convenience of the system, quality of the information, and satisfaction with the electronic communication. All communication requiring interaction between the patient and health care provider will be stored in an activity log. The activity log will be analyzed for frequencies of all patient-provider communication.

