### Adherence to treatment

The number of blood glucose, blood pressure and weight measurements uploaded to the database will be compared to the number of provider-requested measurements. Additionally, it is expected that trending improvement in blood glucose, blood pressure, and weight will be seen.

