### Analysis of data

Data analyses will be facilitated by [name], the bio-statistician on our team, using SAS (Cary, NC) for Windows, version 9.3. For this feasibility and acceptability trial, we will be using a pre/post design. Techniques for assessing differences before and after the mI SMART intervention will depend on the type of outcome. For outcomes which are scaled, i.e., patient-provider satisfaction, the quasi-likelihood analysis will be used to determine if the intervention had an effect on the distribution of scores. For continuous outcomes, i.e., blood glucose, blood pressure, weight, the standard *t* test will be used to test differences in means before and after intervention. If the data are not normally distributed, the non-parametric Wilcoxon rank sum test will be used. For count measures, i.e., patient-provider communication, Poisson regression will be performed to assess the difference in mean counts before and after intervention. For measures that are percentages, i.e., for adherence to treatment measures (as patients will only measure themselves a certain percentage of the prescribed number) logistic regression will be performed to determine the difference pre and post intervention. Each of these analyses will be performed at a significance level of 0.05.

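### Before/after tests are prescribed for upload adherence, technology satisfaction and logged communication, which as defined have no stated value before the intervention

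*Protocol article*

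**What the plan says.** The Sub aim 1b section gives the design: "We will use a pre/post design with no randomization or control group". The sample is fixed by money: "Because of budgetary constraints, we will enroll 30 participants into the study".

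The Analysis of data section places its techniques under differences before and after mI SMART and sorts them by type of outcome:

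- Scaled outcomes, with patient-provider satisfaction named, get a quasi-likelihood analysis of the score distribution.
- Continuous outcomes (glucose, blood pressure, weight) get a t test or a rank test.
- For counts, with patient-provider communication named, "Poisson regression will be performed to assess the difference in mean counts before and after intervention".
- For percentages, with adherence named and explained as the share of prescribed self-measurements actually made, "logistic regression will be performed to determine the difference pre and post intervention".

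It closes: "Each of these analyses will be performed at a significance level of 0.05".

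The measurement sections define the same outcomes as follows:

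- Under Adherence to treatment, the article states: "The number of blood glucose, blood pressure and weight measurements uploaded to the database will be compared to the number of provider-requested measurements".
- Feasibility and acceptability: the team will assess the "acceptability of the technology with post intervention electronic patient and provider satisfaction questionnaires".
- Patient–provider communication and satisfaction: "All communication requiring interaction between the patient and health care provider will be stored in an activity log". The log is then to be tabulated for frequencies.

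**The concern.** A before/after test needs the same quantity measured at two times. For these three outcomes the article defines a measure that comes into being with the platform, or is taken only at the end, and then assigns it a test of change. An analyst following the text would find nothing to put in the first period, or would have to choose a baseline once the data are in hand.

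The abstract already anticipates better communication and better adherence, and a larger randomised trial is to follow from these results. A test that in effect compares using the platform with not yet having it would show only that the system was switched on, yet it could be read as improvement.

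That the article is condensed does not readily explain the gap. It does state baselines elsewhere: the Behavior Score Dashboard (BSD), SF-36v2, UCLA loneliness scale and PHQ-9 are each taken before the intervention and after 12 weeks, and weight, blood pressure and glucose are taken at enrolment.

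**Working it through.** The plan gives no figure to reproduce: 30 is a budget figure without an effect size or a power statement. The check is therefore a comparison of sections, followed by short arithmetic.

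**1. Definition against test**

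| Outcome named in Analysis of data | How it is measured | Value before the intervention | Prescribed test |
|---|---|---|---|
| Adherence (percentage) | Uploads to the study database over requested readings | None: devices and training come from the study (Development of a mobile application; Sub aim 1b) | Pre/post logistic regression |
| Satisfaction (scaled) | Technology questionnaire after the intervention | None stated for this questionnaire | Quasi-likelihood for an effect on the distribution |
| Communication (count) | Activity log, described under Feasibility and acceptability as electronic logs of the applications | No source named | Before/after Poisson regression |
| Glucose, blood pressure, weight | Study devices | Taken at enrolment | t test or rank test |

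Readings taken at enrolment also go to the database. They are the baseline physical values, not a self-monitoring rate, so they do not supply the missing adherence percentage.

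**2. Adherence before the intervention**

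Let A = U / R, with U the uploads and R the requested readings. Before the devices are issued U = 0 and R is not defined, so A is undefined. A single post-intervention value gives a level, not a change.

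**3. What happens if a zero is put in anyway**

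The plan does not say this will be done; the step only shows that it is no way out.

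- Logistic: assume R = 84 (one reading a day, 7 × 12). Then log(0/84) is minus infinity and the fit separates. With assumed post-intervention adherence of 30%, 60% and 90%, the log odds ratio moves from 10.6–13.7 after 10 iterations to 25.6–28.7 after 25. Its standard error goes from 3.9 to about 7,094.
- Poisson: log(mean after / 0) is not finite. With assumed post-intervention means of 2, 10 and 30, the log rate ratio moves from 11.4 to 26.4. Its standard error goes from 6–22 to about 11,000–40,000.

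Neither model has a finite estimate.

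**4. What post-only reporting would deliver with n = 30**

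Wilson 95% interval: [p + z²/2n ± z√(p(1−p)/n + z²/4n²)] / (1 + z²/n), with z = 1.96.

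For p = 0.80: centre = (0.80 + 0.0640)/1.1280 = 0.766, and half-width = 1.96 × √(0.005333 + 0.001067)/1.1280 = 0.139. The interval is 62.7% to 90.5%.

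The observed percentages are assumptions, so here is a range:

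- 50%: 33.2% to 66.8%
- 70%: 52.1% to 83.3%
- 90%: 74.4% to 96.5%

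If only 24 of 30 answered (an assumption), 19/24 = 79% would give 59.5% to 90.8%.

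For a mean, such as the per-participant adherence percentage, the half-width is t(0.975; 29)/√30 = 2.045/5.477 = 0.37 SD. Complete follow-up gives 30 × 12 = 360 participant-weeks for the communication rate.

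**The case against.** Several points on the other side stand:

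- The platform is not the only source of information on these topics. The abstract lists patient self-reports of adherence. Sub aim 1b speaks of activity logging combined with questionnaires for communication and adherence. The BSD covers monitoring and medication taking and is given at both times.
- The communication questionnaire has no stated timing, and most of its items could be asked about usual care.
- The post-intervention timing is stated for acceptability of the technology, while the analysis section names patient-provider satisfaction. The text does not settle whether these are one instrument.
- Feasibility is judged descriptively (presence of data, logs, error messages, number of uses) and does not hang on these tests.

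None of this gives a baseline to the measures actually tested. The logistic model is tied to the share of prescribed self-measurements, and the Poisson model to counts.

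Three stronger readings are tempting but unsupported:

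- A reader might infer that three of the four analysis families cannot be run. The methods are sorted by outcome type. If the named outcomes are illustrations, quasi-likelihood also covers the SF-36v2, UCLA, PHQ-9 and BSD, which have both time points. What fails is its use for technology satisfaction.
- A reader might infer a spurious significant result: one message from each of 30 participants against none gives 2 × 0.5³⁰ = 1.9 × 10⁻⁹. The arithmetic is right, but the plan never says that missing earlier values will be entered as zero.
- A reader might infer that pre-enrolment contacts could never be counted. The Discussion describes a program that extracts data from the clinic's record and scheduling systems, so a source may exist. It is simply not named for this purpose.

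**Conclusion.** The concern holds as a contradiction between the measurement sections and the analysis section, with unequal strength across the three outcomes:

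- Adherence is the clearest. By its own definition it has no pre-intervention percentage, so the prescribed logistic test has no first-period data.
- For technology satisfaction the post-only timing is explicit, so a change in its distribution cannot be estimated. This rests on reading the satisfaction named in the analysis section as that questionnaire.
- For communication the gap is inferred, because the activity log is the only count source named.

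The reach is limited. The t tests keep their enrolment baseline, quasi-likelihood remains usable for the four instruments taken twice, and the descriptive feasibility assessment is untouched. What cannot be supported as written is any claim of statistically tested improvement in upload adherence or system satisfaction, or in logged communication unless a comparable earlier source is named.

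**What to change.** Amend the Analysis of data section before analysis:

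1. **Upload adherence.** Drop the pre/post logistic regression. Report each participant's percentage of requested readings over the 12 weeks, summarised with a 95% confidence interval. Optionally add an early-versus-late change within the 12 weeks, with windows fixed in advance and labelled as persistence of use, not as an effect of the intervention.
2. **System satisfaction.** Drop the test of change and report the post-intervention scores with 95% confidence intervals. Name the SF-36v2, UCLA, PHQ-9 and BSD as the scaled outcomes to which quasi-likelihood applies.
3. **Communication.** Report log-based contacts as a rate per participant-week with a confidence interval. Keep the Poisson before/after comparison only if the same kind of contact is counted from the same source, such as clinic records, in equal windows before and after enrolment. Setting clinic records before against clinic records plus log after would add a channel to one side only. Platform data are to be synchronised into the medical record, so the rule must also prevent double counting.

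Items 1 and 2 cost only wording. Item 3 costs wording plus, if the comparison is kept, one extract from clinic records. The downside is small: no significance test of change for upload adherence and system satisfaction, nor for communication unless the like-for-like comparison is set up.

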### Expected outcomes of Sub aim 1b

The rationale for this aim is that successful completion of the proposed research will contribute a missing, fundamental element to our base of knowledge, without which the feasibility and acceptability of mHealth care delivery in an underserved, rural population will be unknown. The acquisition of such knowledge is critical to the development of improved interventions for at risk rural patients with chronic illnesses. When the proposed studies for sub aim 1b have been completed, it is our expectation that mI SMART will have been found to be feasible and acceptable to rural patients and rural healthcare providers and that overall outcomes of care will have been improved. Such a finding would be of importance because it would constitute a crucial step forward in diminishing health disparities and improving overall health status in underserved populations.

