**Methods:**

Our objective is to provide evidence of feasibility and acceptability for the use of mI SMART in an underserved population and establish evidence for the refinement of mI SMART. The proposed study will take place at Milan Puskar Health Right, a free primary care clinic in the state of West Virginia. The clinic provides health care at no cost to uninsured, low income; adults aged 18–64 living in West Virginia. We will enroll 30 participants into this feasibility study with plans of implementing a longitudinal randomized, comparative effectiveness design in the future. Data collection will include tracking of barriers and facilitators to using mI SMART on patient and provider feedback surveys, tracking of patient-provider communications, self-reports from patients on quality of life, adherence, and self-management ability, and capture of health record data on chronic illness measures.

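### Satisfaction, the acceptability measure, is collected only after the intervention but assigned a before/after test, and no stated criterion links the feasibility data to the expected feasible-and-acceptable finding

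*Protocol article*

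**What the plan says.** The Methods paragraph of the abstract gives the purpose: "Our objective is to provide evidence of feasibility and acceptability for the use of mI SMART in an underserved population". *Sub aim 1b* fixes the design, "We will use a pre/post design with no randomization or control group", the size, "Because of budgetary constraints, we will enroll 30 participants into the study", and the next step, "A larger randomized control trial is planned after analysis of the results of this study".

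*Feasibility and acceptability* lists what will be examined: whether each participant's data are present in the database, activity logs and error messages for participants and providers, and use counts for each application. It then adds: "Lastly, we will assess the acceptability of the technology with post intervention electronic patient and provider satisfaction questionnaires". *Patient–provider communication and satisfaction* adds 5-point Likert items, a rating of satisfaction with the overall system, and frequencies of logged communication. *Adherence to treatment* compares uploaded with provider-requested readings. None of these sections gives a target or cut-off.

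*Analysis of data* is framed around differences before and after the intervention. For scaled outcomes, with satisfaction as its example, it says "the quasi-likelihood analysis will be used to determine if the intervention had an effect on the distribution of scores". It closes: "Each of these analyses will be performed at a significance level of 0.05".

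*Expected outcomes of Sub aim 1b* then states the anticipated finding: "it is our expectation that mI SMART will have been found to be feasible and acceptable to rural patients and rural healthcare providers".

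**The concern.** Two parts of the article do not fit together. One makes satisfaction the measure of acceptability and collects it after the intervention. The other analyses satisfaction as a change from before to after. Satisfaction with a system cannot be scored before the system has been used, and the article states no earlier measurement that could stand in for it.

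Even with a baseline, a change test asks whether scores moved. A significant shift can leave most users dissatisfied, and a non-significant one is compatible with nearly all being satisfied throughout.

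The other feasibility data are reviewed descriptively. That is reasonable for a small uncontrolled study, but nothing says how they lead to the expected finding. At stake is the study's stated objective, which is also the groundwork for the planned randomised trial. If the mark is chosen once the data are known, the same data can support either description.

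**Working it through.** **Stated figures.** There is none to reproduce. The article gives no threshold, power or precision target, and 30 is set by budget.

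**Sections side by side.**

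| Item | Feasibility and communication sections | Analysis of data |
|---|---|---|
| Satisfaction (acceptability) | Post-intervention questionnaire | Before/after change in score distribution, 0.05 |
| Data presence, errors, application use | Reviewed from database and logs | No criterion given |
| Feasible and acceptable | Expected finding | No criterion given |

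The null hypothesis of the satisfaction test is that the score distribution is the same before and after. The acceptability question is whether the proportion satisfied, p, reaches some level p0. Rejecting or retaining the first says nothing about the second.

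**How much an unstated mark matters at n = 30.** Let X be the number of successful or satisfied users, X ~ Binomial(30, p). The chance of meeting a mark r is P(X ≥ r) = Σ from k = r to 30 of C(30,k) p^k (1−p)^(30−k). The marks and true proportions are assumptions, since the article gives none.

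| True p | r = 15 | r = 18 | r = 21 | r = 24 |
|---|---|---|---|---|
| 0.50 | 57% | 18% | 2% | 0.1% |
| 0.60 | 90% | 58% | 18% | 2% |
| 0.70 | 99% | 92% | 59% | 16% |

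**Precision.** Exact (Clopper–Pearson) two-sided 95% intervals run from the 0.025 quantile of Beta(x, 31−x) to the 0.975 quantile of Beta(x+1, 30−x):

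- 18/30: 41% to 77%
- 21/30: 51% to 85%
- 24/30: 61% to 92%

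**What a pre-set floor would require.** The one-sided 95% exact lower bound is the 0.05 quantile of Beta(x, 31−x).

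- Floor 50%: 19/30 gives 46.7% and fails; 20/30 gives 50.06% and passes. P(X ≥ 20) is 4.9% at p = 0.50, 73% at 0.70 and 97% at 0.80.
- Floor 60%: 22/30 gives 57.0% and fails; 23/30 gives 60.6% and passes. P(X ≥ 23) is 4.4% at p = 0.60 and 76% at 0.80.

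**Two criteria together.** If use and satisfaction must both reach 20/30 and are independent (an assumption), the chance of passing both is 0.730² = 53% at a true 70% and 0.974² = 95% at a true 80%. Positive dependence would bring these closer to the single-criterion figures.

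**The case against.** The strongest reply is that this is a condensed article. Numeric progression cut-offs are the kind of detail a full protocol or analysis plan may hold, and a 30-person study may properly be descriptive. The abstract's aim is to provide evidence and refine the system, which is estimation and learning and does not demand a pass/fail verdict. All of this stands, and a missing pass mark alone would not be a finding. What remains is internal to the article: it names a test for satisfaction that does not match when satisfaction is measured or what acceptability asks.

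Three stronger readings are tempting and are not supported.

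- A reader might infer that p < 0.05 is the rule for declaring the system feasible. No section says so. The 0.05 level is attached to the before/after tests, and feasibility has its own descriptive section.
- A reader might infer that no result could lead to a negative conclusion. Missing data, logged errors or poor ratings could all support one. The accurate statement is that no pre-specified result would.
- A reader might want to put a figure on how often the change test would give the wrong acceptability verdict. That needs assumed means and standard deviations, a baseline score the article does not describe, and an equation of significance with acceptability that it never makes.

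The larger trial is planned after the analysis of results; it is not stated to be conditional on them.

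**Conclusion.** The point holds in a limited form. The analysis named for satisfaction has no stated pre value, and a change test could not show whether satisfaction is high enough. The descriptive feasibility measures are not tied by any stated criterion to the expected finding. The size of the problem can only be illustrated: at a true 60%, the chance of meeting a mark runs from 90% (15/30) to 2% (24/30), so a mark chosen afterwards could settle the description. This assumes 30 independent participants with binary outcomes, and the marks are assumptions. A fuller protocol or analysis plan may contain criteria. The correction should be made, with medium confidence.

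**What to change.** In *Analysis of data*:

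1. Remove satisfaction from the before/after tests and keep those tests for outcomes of care only.
2. Report the post-intervention proportion rating overall satisfaction 4 or 5, with all 30 enrolled as the denominator and an exact confidence interval. This assumes the overall item uses the 5-point scale given for the communication items; the article should say so.
3. Report in the same way the proportion reaching a system-use level set in advance, expressed relative to each participant's provider-requested readings because monitoring goals are patient-specific.
4. Compare each lower bound with a floor the sponsor fixes before data are seen. As examples only, a one-sided 95% exact bound above 50% needs at least 20/30, and above 60% at least 23/30. Otherwise the result is to refine before the randomised trial.
5. Report provider satisfaction descriptively, and limit the conclusion about providers in *Expected outcomes of Sub aim 1b* accordingly.

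The cost is wording plus the choice of floors and use level. The data are already planned, and no extra participants or visits are needed. The downside is that the study can return a refine-first result: with the 20/30 mark each criterion passes 73% of the time at a true 70% and 97% at a true 80%, and the chance of passing both is lower.

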The team has completed several intervention studies in addition to two preliminary studies at the free clinic proposed for use in this study. The first study at this clinic was an intervention study that involved testing the effectiveness of Group Medical Visits (GMVs) with a sample of 111 patients with a chronic illness receiving care at the rural free clinic. The intervention, intended to cluster care, included group education and elements of an individual patient visit. There were 53 participants who attended GMVs and 58 participants who received usual care. The majority of patients were female, white, morbidly obese, had a high-school education or less, were age 50 or younger, had a mean of 5 co-morbid conditions, and drove long distances to receive care. At baseline, the patients who attended GMVs had higher A1C levels, reported more pain, had increased depression levels and were more obese than those who received usual care. There was a statistically significant decrease in systolic blood pressure from time one to time two in patients who attended GMVs. There was no significant impact on outcomes of patients who received usual care from time one to time two. However, it is important to note that the majority of patients attended two or fewer visits in 1 year. Previous studies reviewed related to GMVs suggest that improved interventions are seen in those patients who attend more frequently (Trento et al. 2001, 2002; Beck et al. 1997). Hence, the lack of improvement in biophysical outcomes of care in this sample of patients who attended GMVs may be due to low attendance rates. The limited impact of this traditional style intervention in relation to low attendance argues for the need to test alternative interventions to reach this difficult population.

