Although there is little ethnic diversity in West Virginia, we have a unique opportunity to study a vulnerable and understudied group. Because samples from most clinical studies are recruited from healthcare providers at medical centers, a notably under-studied group has been those who are uninsured or underinsured and receive low cost and free care. Yet, it is precisely this group, who usually has multiple chronic illness and many barriers to self-management that is of interest to researchers and healthcare providers as they attempt to reduce health disparities. By collaborating with Health Right, we have an opportunity to enroll these individuals and thus include a heretofore “hard-to-reach” population. By using community healthcare providers and based on our previous work, we anticipate high rates of identification, recruitment and retention of this underserved population living in a highly distressed environment. In addition, our experience suggests that we will enroll roughly equal numbers of women and men, and will have no trouble including women, thus, providing us with the opportunity for meaningful, comparisons between men and women. We also will enroll adults between the ages of 18–64, an understudied group when looking at chronic illness.

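### An uncontrolled 30-person before/after feasibility study tests its outcomes at 0.05 each and reads change as an effect of mI SMART, which the design cannot show

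*Protocol article*

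**What the plan says.** The Sub aim 1b section of the protocol article fixes the design: "We will use a pre/post design with no randomization or control group". It sets the size by money: "Because of budgetary constraints, we will enroll 30 participants into the study". Besides feasibility and acceptability, it lists as outcomes of care "patient–provider communication, adherence to treatment, self-management ability, quality of life, blood glucose, blood pressure, and weight". None is called primary. Loneliness and depression are added under Quality of life and functional ability, which also describes the SF-36v2 as covering eight health concepts.

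Analysis of data assigns a significance test to each type of outcome: scaled, continuous, count and percentage. For scaled outcomes, the quasi-likelihood analysis "will be used to determine if the intervention had an effect on the distribution of scores"; for the other types the text speaks of differences before and after. It closes: "Each of these analyses will be performed at a significance level of 0.05".

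Expected outcomes of Sub aim 1b states the expectation that mI SMART will prove feasible and acceptable and that "overall outcomes of care will have been improved", and treats such a finding as a crucial advance against health disparities. The Conclusion expects about equal numbers of women and men, "providing us with the opportunity for meaningful, comparisons between men and women".

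**The concern.** The stated objective is feasibility and acceptability, but the analysis section is made up of before/after significance tests, and the expected result includes better outcomes. Three things stand between those tests and that result.

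- **No control.** Any change over 12 weeks includes whatever would have happened without mI SMART.
- **Several tests, each at 0.05, none given priority.** Some nominally significant changes can be expected by chance, and nothing in the text says which result would count.
- **A subgroup claim far beyond the sample size.** About 15 people of each sex cannot give an informative comparison.

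At stake is how the results will be used. The section on the intervention says that preliminary data from this study will feed the next grant application, and Sub aim 1b says that a larger randomised trial will follow. A change read as an effect here would pass into the rationale and assumptions of that trial.

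**Working it through.** The sample size of 30 comes with no power, effect size or SD, so there is no statistical figure of the plan's own to reproduce. The checks below use the stated 30 people and 0.05 per test. Two-sided testing is assumed, because the text does not say.

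**1. How many tests?** The text does not give a number, so three counts are used.
- Outcomes named in Analysis of data: satisfaction, communication, adherence, glucose, systolic pressure, diastolic pressure, weight = 7 (6 if blood pressure is one outcome).
- All outcomes measured, with the SF-36 as one score and blood pressure as one outcome: satisfaction, communication, adherence, self-management, SF-36, loneliness, PHQ-9, glucose, blood pressure, weight = 10. Splitting blood pressure in two and adherence in three gives 13.
- Clinical and questionnaire scores only, with eight SF-36 scales: 8 + loneliness + PHQ-9 + self-management + glucose + systolic + diastolic + weight = 15. Adding satisfaction, communication and adherence gives 18, or 20 with adherence split in three.

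**2. Chance of at least one false positive with no true change.** For k independent tests, either direction: 1 − 0.95^k. For a false improvement only, each two-sided test contributes 0.025: 1 − 0.975^k.

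| k | Either direction | False improvement |
|---|---|---|
| 7 | 1 − 0.698 = 30% | 1 − 0.838 = 16% |
| 10 | 1 − 0.599 = 40% | 1 − 0.776 = 22% |
| 15 | 1 − 0.463 = 54% | 1 − 0.684 = 32% |

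For 20 tests the either-direction figure is 64%. Scores from the same 30 people are likely to be correlated. A simulation of 200,000 draws of equally correlated two-sided z tests gives, in either direction at correlations of 0.3, 0.5 and 0.7:
- 10 tests: 35%, 29%, 21%
- 15 tests: 46%, 36%, 26%

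**3. Is 30 too small for a single before/after test?** Not in itself. A paired t test in 30 people has about 75% power for a mean change of 0.5 SD of the differences (noncentral t, no dropout). The obstacle to the inference is the lack of a control, and then multiplicity, rather than the power of each test.

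**4. Men versus women.** With 15 per sex and 80% power, the normal approximation gives d = (1.960 + 0.842) × √(2/15) = 2.802 × 0.365 = 1.02. The noncentral t gives 1.06. Power at an assumed d of 0.5 is 26% by t, and at 0.8 it is 56%. For d = 0.5 with 80% power, n per sex = 2 × 2.802² / 0.5² = 62.8, so 63 per sex or 126 in all, against 30 enrolled.

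**5. Attribution.** No calculation removes this problem. With one group, observed change = effect of mI SMART + time trend + effect of other care + any regression to the mean. The design estimates only the sum.

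**The case against.** The strongest defence is that the article is open about what it is. It states a feasibility objective, says plainly that there is no control, and defers the controlled comparison to a later randomised trial. The section on expected outcomes voices an expectation, and no rule turns a p-value into a claim of effectiveness. Naming a primary outcome and handling multiplicity are often left to a fuller protocol or analysis plan, which is not shown.

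Much of this stands, and it limits how far the point can go. Several stronger readings are tempting, but the text does not support them:

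- *At least 15 tests are planned, and a false improvement is more likely than not.* Analysis of data names only 6 or 7 outcomes, and nothing says that eight SF-36 scales will be tested separately. The 54% covers both directions; for improvement it is 32%. Passing 50% would take 28 independent tests (ln 0.5 / ln 0.975 = 27.4).
- *The study plans to conclude that outcomes improved.* It expects this; it does not set it as a planned conclusion.
- *Poorly controlled patients are selected, so regression to the mean will flatter the result.* Eligibility rests on distance, diagnosis, age and attendance at the clinic. Nurse practitioners recommend patients, but no control criterion is stated. Regression to the mean is possible, and its size cannot be derived from the document.
- *A sex comparison is planned, and the equal split contradicts earlier data.* The Conclusion mentions an opportunity; Analysis of data contains no analysis by sex. The Discussion says of one earlier study of 111 patients, "The majority of patients were female, white, morbidly obese", but gives no percentage, and a majority can be close to half.

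The defence does not reach the core. An unseen analysis plan could add a multiplicity method, but not a control group. The article itself fixes 0.05 for each analysis, uses the language of effect, and calls the sex comparison meaningful.

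**Conclusion.** The point holds in a limited form: the effect and improvement wording goes beyond what a single-group study of 30 can show. The lack of a control is decisive and needs no assumption.

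Multiplicity is secondary. The chance of at least one false positive in either direction is 30% to 54% for 7 to 15 independent tests, and for a false improvement 16% to 32%. These figures assume two-sided tests and no true change. Correlation lowers them, but at 10 or 15 tests even a correlation of 0.7 leaves the either-direction figure at 21% or 26%, well above 5%.

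The claim of meaningful comparisons between the sexes fails on size: about 1.06 SD is needed for 80% power, assuming 15 per sex and no dropout. An uneven split or dropout would make this worse.

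This should be corrected, but it does not undermine the study as a test of feasibility and acceptability.

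**What to change.** - **Analysis of data and Expected outcomes of Sub aim 1b:** state that the study's conclusion rests on feasibility and acceptability.
- **Analysis of data:** report clinical and questionnaire changes as exploratory estimates with 95% confidence intervals, for use in planning the randomised trial. Replace the language of intervention effect with change from before to after.
- **Expected outcomes of Sub aim 1b:** remove the expectation that outcomes of care will be shown to have improved.
- **Conclusion:** describe any comparison of men and women as descriptive only.

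The cost is a few sentences and a weaker headline claim; data collection does not change.

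A comparison with clinic-record values in non-enrolled distant patients might look like a cheap substitute for a control, but it is not recommended. Study readings come from the supplied devices, many of them at home. The team's own record study found that 42% of scheduled patients did not attend, so clinic values would be selectively missing. Non-enrolled patients would also not have been through the nurse practitioners' recommendation.
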